## Abstract

**Introduction::**

Interventional ablation has been demonstrated to represent an effective therapy in patients with atrial fibrillation (AF), leading to restoration and maintenance of sinus rhythm in the majority of cases. However, recurrence of AF is encountered in 35% to 40% of cases, and the causes for this frequent complication have not been elucidated so far.

**Material and methods::**

Here we present the study protocol of the FIBRO-RISK trial, a prospective, single-center, cohort study which aims to investigate the impact of inflammatory-mediated myocardial fibrosis on the risk of recurrence after successful catheter ablation of atrial fibrillation. The level of systemic inflammation in the pre-ablation and immediate post-ablation period will be assessed on the basis of serum levels of inflammatory biomarkers (hsCRP, matrix metalloproteases, interleukin-6), while the level of cardiac fibrosis will be determined based on cardiac magnetic resonance imaging associated with complex post-processing techniques for mapping myocardial fibrosis at the level of left atrium and left ventricle. At the same time, the amount of epicardial fat will serve as an indirect marker of localized inflammation and will be determined at different levels in the heart (surrounding left atrium, right atrium or the entire heart), while ventricular function will be assessed on the basis of serum levels of NT-proBNP prior to the procedure. All these parameters will be investigated in patients with successful ablation of AF, who will be divided into 2 groups: group 1 – patients who develop AF recurrence at 1-year, and group 2 – patients with no recurrence of AF at 1-year. In all patients, the following biomarkers will be determined: serum levels of inflammatory biomarkers and NT-proBNP at 24 hours and 1-year post procedure, the amount of myocardial fibrosis at the level of left atrium and left ventricle at baseline +/− 7 days, and the amount of epicardial fat surrounding left atrium, right atrium and the entire heart at baseline +/− 7 days.

The primary endpoint of the study will be represented by the rate of AF recurrence at 1-year post ablation, documented by either ECG or Holter monitoring. The secondary endpoints of the study will consist in:

In conclusion, FIBRO-RISK will be the first CMR-based study that will investigate the impact of inflammation-mediated myocardial fibrosis and ventricular remodeling on the risk of recurrence after successful ablation of AF, aiming to validate inflammatory biomarkers and myocardial fibrosis as predictors for AF recurrence.

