### Background and rationale

1.1

Atrial fibrillation (AF) has an increasing prevalence, being currently the most frequent type of supraventricular arrhythmia and representing a significant burden for the healthcare system. In most of the cases, myocardial tissue located at the level of the pulmonary veins represents the origin of AF. The pathophysiology of AF is still incompletely understood, several studies suggesting that profibrotic and inflammatory processes can play a crucial role in the development of AF.^[1]^ So far the success rate of AF ablation is not very high, reaching 70% in patients with paroxysmal AF and 50% in cases with persistent AF. Several risk factors for the occurrence and recurrence of AF have been described in the literature, including left atrial (LA) enlargement, left ventricular (LV) dysfunction, the amount of epicardial fat surrounding cardiac structures, or myocardial fibrosis.^[2]^ However, the relationship between inflammatory-mediated myocardial fibrosis and AF recurrence after radiofrequency catheter ablation has not been elucidated so far.^[3]^

Here we present the study protocol of the FIBRO-RISK trial, a prospective, single-center, cohort study which aims to investigate the impact of inflammatory-mediated myocardial fibrosis on the risk of recurrence after successful catheter ablation of AF.

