### Study population

2.3

The study will include 100 subjects with AF suitable for catheter ablation. Imaging biomarkers and laboratory analyses such as: high sensitive C Reactive Protein (hsCRP), matrix metalloproteases (MMPs), interleukin-6 (IL6) and N-Terminal Pro–B-Type Natriuretic Peptide (NT pro-BNP) will be determined in the first 24 hours after the procedure. The anatomy of pulmonary veins, atrial fibrosis, atrial volumes and the amount of epicardial fat will be evaluated and quantified with late gadolinium-enhancement cardiac magnetic resonance (LGE-CMR). All these parameters will be investigated in patients with successful ablation of AF, who will be divided into 2 groups: group 1 – patients who develop AF recurrence at 1 year, and group 2 – patients with no recurrence of AF at 1 year. In all patients, the following biomarkers will be determined: serum levels of inflammatory biomarkers and NT-proBNP at 24 hours and 1-year post procedure, the amount of myocardial fibrosis at the level of left atrium and left ventricle at baseline +/− 7 days, and the amount of epicardial fat surrounding left atrium, right atrium and the entire heart at baseline +/− 7 days.

The study will be conducted over a period of 2 years, in which patients will be examined at baseline, and will be followed-up for recurrence of AF, as shown by the FIBRO-RISK diagram with the flowchart that will be used in the study (Fig. 1).

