**Figure 1 F1:**
[figure not shown]
Flowchart diagram of FIBRO-RISK study. hs-CRP = high sensitivity C reactive proteine, IL-6 = Interleukine 6, LGE – CMR = late Gadolinium enhancement CMR, MMPs = matrix metalloproteinases, TTE = transthoracic echocardiography.

Inclusion criteria:

Patients with non-valvular paroxysmal or persistent AF who undergo successful catheter ablation, either by cryoablation or by radiofrequency advanced 3D mapping system;Ability to provide informed consent;Patients aged at least 18 years;

Exclusion criteria:

Patients with valvular AF;Patients with acute coronary syndrome in the last 30 days;Patients in whom AF is presumed to be caused by hyperthyreosis;Patients with long-standing persistent or permanent AF;Unwillingness or incapacity to provide informed consent;Allergy to gadolinium contrast media;Absolute or relative contraindications to magnetic resonance imaging;Pregnancy or lactation;Women with childbearing potential in absence of any contraceptive treatment;Renal insufficiency (creatinine greater than 1.5 mg/dL) or renal failure requiring dialysis;Active malignancy or malignancy within the last 5 year prior to enrollment;Conditions associated with an estimated life expectancy of under 2 years;

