#### Biomarkers assays

2.6.1

Complete blood count and biochemistry will be evaluated at the central laboratory of the County Clinical Emergency Hospital of Tirgu Mures as per routine clinical practice, at baseline.

Inflammatory status will be assessed at baseline, respectively at 1-year post procedure. hsCRP levels will be assayed by immunoturbidimetric assay (COBAS INTEGRA 400 plus Analyser, Roche Diagnostics, Switzerland). Matrix metalloprotease 9 and interleukin-6 levels will be assessed via enzyme immunoassay (ELISA) method (Dynex DSX Automated ELISA System, Dynex Technologies, USA; IMMULITE 2000 XPi Immunoassay System, Siemens, USA). Determination of all inflammatory biomarkers will be performed at the Advanced Medical and Pharmaceutical Research Center of the University of Medicine and Pharmacy Targu-Mures. NT-proBNP serum levels will be determined prior to the procedure, at 24 hours, and repeated after 1 year, at the central laboratory of the Emergency Clinical County Hospital of Tirgu-Mures using an electrochemiluminescent immunoassay (IMMULITE 2000 XPi Immunoassay System, Siemens, USA).

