Beside baseline evaluation, several studies suggest that quantification of post ablation LA scarring may play a role in determination of the AF recurrence risk.^[10]^ Several recent studies managed to assess the feasibility of LGE-MRI in detecting both pre-existing and post-ablation atrial and ventricular fibrosis.^[8,11–14]^ Their results raised interest in the use of CMR as a periprocedural risk assessment tool. Despite these promising results, the assessment of atrial and ventricular fibrosis has not yet been widely adopted in clinical practice.^[15–18]^ We should not forget that the capacity of LGE-CMR to detect fibrosis in the atria is still controversial due to the lack of reproducibility. Thus, this trial aims to validate myocardial fibrosis, targeting both atrial and ventricular fibrosis quantified by CMR, as predictor for AF recurrence.

Previous observational studies showed that elevation of several inflammatory serum biomarkers, such as hsCRP or IL-6, are associated with occurrence and recurrence of AF, since patients with AF present significantly higher levels of inflammatory biomarkers as compared with subjects maintaining sinus rhythm.^[3,19–22]^ Therefore, the role of inflammation in AF recurrence has been recently proposed as a new and challenging hypothesis to explain the high rate of recurrence after AF conversion.^[3,21,23–26]^ As the exact pathways from inflammation to AF are still unclear, it is presumed that inflammatory cytokines may bind to atrial myocytes inducing tissue damage.^[24]^ In line with this hypothesis, the FIBRO-RISK trial aims to investigate the correlation between inflammatory biomarkers and cardiac fibrosis, evaluated via LGE-CMR, in order to prove the impact of inflammatory-related myocardial fibrosis on the risk of recurrence after successful catheter ablation of AF.

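### Unadjusted marker comparisons cannot support the claim of independent prediction, because AF type (and possibly rhythm at the draw) can link a marker to recurrence

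*Protocol article*

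**What the plan says.** - **Reading of the markers.** The abstract says that "ventricular function will be assessed on the basis of serum levels of NT-proBNP prior to the procedure". Section 2.6.1 says "Inflammatory status will be assessed at baseline, respectively at 1-year post procedure". Neither sentence refers to AF type or to rhythm when blood is taken.
- **Cohort.** The inclusion criteria in section 2.3 admit "Patients with non-valvular paroxysmal or persistent AF who undergo successful catheter ablation".
- **Prognosis by AF type.** Section 1.1 gives ablation success as "reaching 70% in patients with paroxysmal AF and 50% in cases with persistent AF". The abstract adds that "recurrence of AF is encountered in 35% to 40% of cases".
- **Markers and AF.** The Discussion (section 3) reports that "patients with AF present significantly higher levels of inflammatory biomarkers as compared with subjects maintaining sinus rhythm".
- **Analysis.** Section 2.13 names the t test, the Mann-Whitney test and Fisher's exact test for two-group comparisons, and no adjusted or stratified method.
- **Intended inference.** The Discussion aims to validate ventricular remodeling, serum markers and fibrosis as independent predictors of recurrence, and to show that inflammation has a role.
- **Draw times.** Section 2.6.1 says "NT-proBNP serum levels will be determined prior to the procedure, at 24 hours, and repeated after 1 year". Section 2.3 says the laboratory markers and NT-proBNP "will be determined in the first 24 hours after the procedure". The abstract lists both at 24 hours and 1 year. The baseline blood list in section 2.9 includes the inflammatory markers but not NT-proBNP.

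**The concern.** AF type is prognostic on the article's own figures, and the groups being compared are defined by recurrence. Persistent AF will therefore be over-represented among patients who recur. If a marker is higher in persistent AF, or in patients who are in AF when blood is drawn, it will differ between the recurrence groups even if it carries no information about recurrence within either AF type. The tests in section 2.13 cannot separate that route from an effect of inflammation.

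At stake is the specific claim of the study. A significant unadjusted difference in IL-6 or hsCRP could be reported as evidence that inflammation drives recurrence when it partly reflects which patients had persistent AF. The word independent needs an analysis that holds at least the obvious prognostic factor constant.

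**Working it through.** The article gives no figure for this effect, so there is none to reproduce. The power statement in section 2.12 does not bear on it.

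**Inputs from the article.** Recurrence of 0.30 in paroxysmal and 0.50 in persistent AF (one minus the success rates in section 1.1, treated as 1-year recurrence); overall recurrence R of 0.35 to 0.40 (abstract); n = 100; two-sided 5% level.

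**Assumptions not in the article.** The marker is raised by d = 0.5 or 1.0 SD in patients in AF at the draw. The proportions in AF at the draw are either 100% of persistent and 0% of paroxysmal patients (full separation) or 80% and 20%. Within AF type the marker is unrelated to recurrence.

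**Step 1: persistent share f.** R = 0.30(1 − f) + 0.50f, so f = (R − 0.30)/0.20. R = 0.35 gives f = 0.25; R = 0.40 gives f = 0.50.

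**Step 2: persistent AF within each recurrence group.** Among recurrers a = 0.50f/R; among non-recurrers b = 0.50f/(1 − R).
- f = 0.25: a = 0.125/0.35 = 35.7%, b = 0.125/0.65 = 19.2%, a − b = 0.165.
- f = 0.50: a = 0.25/0.40 = 62.5%, b = 0.25/0.60 = 41.7%, a − b = 0.208.

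**Step 3: spurious gap between groups.** Gap = d × (P[in AF | persistent] − P[in AF | paroxysmal]) × (a − b), in units of the SD among patients in the same rhythm.

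**Step 4: rejection rate.** With q the proportion in AF at the draw in each recurrence group, SE² = [1 + d²q₁(1 − q₁)]/(100R) + [1 + d²q₂(1 − q₂)]/[100(1 − R)]. With k = gap/SE, the rate is approximately Φ(k − 1.96) + Φ(−k − 1.96).

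Example (f = 0.50, d = 1.0, full separation): gap = 0.208; SE² = 1.234/40 + 1.243/60 = 0.0516, SE = 0.227; k = 0.917; rate = Φ(−1.043) + Φ(−2.877) = 0.149 + 0.002 = 15.1%.

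| Persistent share | In AF at draw (persistent / paroxysmal) | d | Gap (SD) | Rejection rate |
|---|---|---|---|---|
| 25% | 100% / 0% | 0.5 | 0.08 | 6.7% |
| 25% | 100% / 0% | 1.0 | 0.16 | 11.1% |
| 50% | 100% / 0% | 0.5 | 0.10 | 7.9% |
| 50% | 100% / 0% | 1.0 | 0.21 | 15.1% |
| 25% | 80% / 20% | 0.5 | 0.05 | 5.6% |
| 25% | 80% / 20% | 1.0 | 0.10 | 7.1% |
| 50% | 80% / 20% | 0.5 | 0.06 | 6.0% |
| 50% | 80% / 20% | 1.0 | 0.13 | 8.5% |

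A simulation of 20,000 trials per setting with the planned t test agreed with these rates to within about 0.4 percentage points. Adding AF type to the comparison brought the rate to between 4.7% and 5.3% in every setting. That is expected, since recurrence in the simulation depends on AF type alone. With weaker separation (80% and 30% in AF) the unadjusted rate is 5.4% to 7.4%, so the effect becomes small when AF type says little about rhythm at the draw.

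**The case against.** **NT-proBNP.** A reader might infer that pre-procedure NT-proBNP merely records whether the patient was in AF that day. The article does not say that NT-proBNP rises with rhythm; the Discussion calls it a marker of ventricular dysfunction. That part is an assumption and carries no weight here. Nor does ventricular function rest on NT-proBNP alone: ejection fraction is measured by echocardiography (section 2.6.2) and CMR (section 2.6.3). Only the abstract sentence needs repair.

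**Rhythm at the draw.** The Discussion sentence on inflammatory markers compares kinds of patient. It does not say that a marker moves with rhythm when blood is taken, and the article does not say what rhythm either AF type is in on day 0. This objection stands. The confounding route through AF type needs only that the marker differs by AF type.

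**Size.** It is tempting to conclude that the study would report a false result. The calculation does not support that: even under full separation with a 1.0 SD shift, about 85% of studies would show no spurious difference in a given marker.

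**Timing.** The AF-type link to rhythm is most plausible before the procedure. Some passages place the draw within 24 hours after a successful ablation, where that link has no support in the article.

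**Level of detail.** A covariate list may sit in an unseen analysis plan, and for a prediction panel a marker that tracks AF type still predicts. Both are fair. The point does not depend on a missing list, however: section 2.13 states a method, the Discussion states an inference, and that method cannot deliver that inference.

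**Conclusion.** The concern holds in a limited form. The stated unadjusted tests do not support a claim of independent prediction in a cohort that mixes two AF types with recurrence of about 30% and 50%. For the inflammatory markers, the article's own statement that they are higher in patients with AF makes the confounding route credible. The inflation is modest: roughly 6% to 15% false positives per marker against a nominal 5%, for shifts of 0.5 to 1.0 SD and a persistent share of 25% to 50%. The upper end requires AF type and rhythm at the draw to coincide completely. The shift, the share, rhythm at the draw and any similar behaviour of NT-proBNP are all assumptions. The change is worth making because it is cheap and bears on the main claim of the study.

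**What to change.** 1. In section 2.13, compare each baseline marker between recurrence groups adjusted for or stratified by AF type, for example with a stratified rank test or a logistic model for recurrence containing the marker and AF type. The unadjusted comparison can stay as description.
2. For the baseline draw, add rhythm on the day-0 12-lead ECG, unless it nearly duplicates AF type. For other draws, use rhythm only where an ECG exists. Sections 2.6 and 2.9 schedule ECGs at baseline and months 1, 3, 6 and 12; none is listed for the 24-hour draw, or for a CMR done up to 7 days from baseline.
3. Reword the abstract so that ventricular function rests on the echocardiographic and CMR ejection fraction, with NT-proBNP reported as a separate marker.
4. Reconcile the blood-draw times in the abstract and sections 2.3, 2.6.1 and 2.9, and state which draw is the predictor.

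Cost: one or two model terms and wording changes, using baseline data already planned. There is a small loss of precision if rhythm and AF type nearly coincide, in which case AF type alone is enough.

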## Introduction

1

### Background and rationale

1.1

Atrial fibrillation (AF) has an increasing prevalence, being currently the most frequent type of supraventricular arrhythmia and representing a significant burden for the healthcare system. In most of the cases, myocardial tissue located at the level of the pulmonary veins represents the origin of AF. The pathophysiology of AF is still incompletely understood, several studies suggesting that profibrotic and inflammatory processes can play a crucial role in the development of AF.^[1]^ So far the success rate of AF ablation is not very high, reaching 70% in patients with paroxysmal AF and 50% in cases with persistent AF. Several risk factors for the occurrence and recurrence of AF have been described in the literature, including left atrial (LA) enlargement, left ventricular (LV) dysfunction, the amount of epicardial fat surrounding cardiac structures, or myocardial fibrosis.^[2]^ However, the relationship between inflammatory-mediated myocardial fibrosis and AF recurrence after radiofrequency catheter ablation has not been elucidated so far.^[3]^

Here we present the study protocol of the FIBRO-RISK trial, a prospective, single-center, cohort study which aims to investigate the impact of inflammatory-mediated myocardial fibrosis on the risk of recurrence after successful catheter ablation of AF.

### Study objectives

1.2

The *primary objective* of the study is to investigate the correlation between the degree of LA and LV fibrosis quantified by cardiac magnetic resonance (CMR), inflammatory biomarkers, and the risk of AF recurrence post catheter ablation.

The *secondary objective* of the study is to investigate the correlation between structural remodeling of the left and right atrium, epicardial fat tissue volume and serum inflammatory biomarkers in patients with AF undergoing successful catheter ablation and their impact on long term outcomes.

## Methods/design

2

### Study design

2.1

This is a clinical prospective, non-randomized, cohort, single-center study to investigate the relationship between inflammatory status, inflammation-mediated atrial and ventricular fibrosis and remodeling, and the risk of AF recurrence. The duration of the study is 2 years which include the initial screening and the follow-up period for the recurrence of AF.

### Ethics

2.2

The study protocol was approved by the Ethics Committee for Scientific Research of the University of Medicine and Pharmacy of Tirgu Mures (certificate of approval: 346/13.12.2017) and the Ethics Committee for Scientific Research of the Cardio Med Medical Center (certificate of approval 28/10.06.2018). All study procedures comply with the *Declaration of Helsinki* of 1975, and all patients will sign an informed consent and will be checked for the inclusion and exclusion criteria prior to enrollment in the study.

### Study population

2.3

The study will include 100 subjects with AF suitable for catheter ablation. Imaging biomarkers and laboratory analyses such as: high sensitive C Reactive Protein (hsCRP), matrix metalloproteases (MMPs), interleukin-6 (IL6) and N-Terminal Pro–B-Type Natriuretic Peptide (NT pro-BNP) will be determined in the first 24 hours after the procedure. The anatomy of pulmonary veins, atrial fibrosis, atrial volumes and the amount of epicardial fat will be evaluated and quantified with late gadolinium-enhancement cardiac magnetic resonance (LGE-CMR). All these parameters will be investigated in patients with successful ablation of AF, who will be divided into 2 groups: group 1 – patients who develop AF recurrence at 1 year, and group 2 – patients with no recurrence of AF at 1 year. In all patients, the following biomarkers will be determined: serum levels of inflammatory biomarkers and NT-proBNP at 24 hours and 1-year post procedure, the amount of myocardial fibrosis at the level of left atrium and left ventricle at baseline +/− 7 days, and the amount of epicardial fat surrounding left atrium, right atrium and the entire heart at baseline +/− 7 days.

The study will be conducted over a period of 2 years, in which patients will be examined at baseline, and will be followed-up for recurrence of AF, as shown by the FIBRO-RISK diagram with the flowchart that will be used in the study (Fig. 1).

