### Sample size

2.12

The study will include 100 subjects with AF undergoing successful ablation of pulmonary veins via interventional route. After analysis of follow-up data, patients will be distributed in two groups according to the presence or absence of recurrent episodes of AF during the follow-up.

Sample size calculation was performed using the StatMate 2.0 software. For sample calculation, the proportion of event-free population was estimated at 60%. According to this calculation, a sample size of 50 patients in each subgroup has a 90% power to detect an increase in MACE-free rates proportion of 0.29, with a significance level (alpha) of 0.05 (2-tailed). Therefore, the total sample size was established at 100 patients.

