## Discussion

3

This study presets the protocol of a prospective, single-center, cohort study which aims to investigate the impact of inflammatory-mediated myocardial fibrosis on the risk of recurrence after successful catheter ablation of AF.

Although AF ablation procedures are constantly improving, recurrences continue to be problematic as a significant proportion of patients present with AF relapse despite an optimum management in the post-ablation period.^[1,4]^ In the latest years, a large number of studies tried to identify predictors for a successful outcome on long term after AF ablation, however reliable clinical markers to predict sinus rhythm maintenance or AF recurrence have not been identified so far. The main contribution of the present study will be to validate new clinical features, such as inflammatory biomarkers, epicardial fat, ventricular remodeling or myocardial fibrosis, as predictors of AF recurrence in patients who are scheduled for catheter ablation. In this trial we hypothesize that several imaging markers associated with cardiac structural alteration, provided by CMR (such as LA, LV fibrosis, atrial volumes or the amount of epicardial fat), associated with serum inflammatory biomarkers (IL-6, MMP-9, hsCRP) could form a powerful prediction panel to predict the risk of AF recurrence in the post ablation period, reflecting the impact of inflammatory-mediated myocardial fibrosis on the risk of arrhythmia.

The relationship between inflammation, myocardial injury and atrial fibrillation has been extensively studied in the recent years.^[5]^ It is well known that a higher amount of atrial fibrotic tissue can favor atrial arrhythmogenesis.^[2,6]^ At the same time, the amount of contrast enhancement in the LA wall, considered to represent the volume of fibrotic tissue of the total LA wall, has been recently described by prospective trials to be independently associated with the likelihood of recurrent arrhythmia after ablation.^[2,6,7]^ Previous studies showed that pre-existing fibrosis on LGE-CMR was the strongest independent predictor of ablation procedure failure and arrhythmia recurrence.^[8]^ McGann et al proved that subjects with >30% atrial fibrosis on LGE images at baseline had a 71% chance of AF recurrence at 1 year.^[9]^

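### The article gives incompatible sampling times for the inflammatory biomarkers and NT-proBNP, and one version leaves no pre-ablation value for a predictor in the primary objective

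*Protocol article*

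**What the plan says.** Sampling times appear in four places of the protocol article.

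- **Abstract, Material and methods.** It opens with "The level of systemic inflammation in the pre-ablation and immediate post-ablation period will be assessed", which means both periods. It places NT-proBNP before the procedure. Its later list then gives the inflammatory markers and NT-proBNP at 24 hours and 1 year.
- **Section 2.3, Study population.** The laboratory markers, NT-proBNP included, "will be determined in the first 24 hours after the procedure". The section then lists, for all patients, "serum levels of inflammatory biomarkers and NT-proBNP at 24 hours and 1-year post procedure".
- **Section 2.6.1, Biomarkers assays.** "Inflammatory status will be assessed at baseline, respectively at 1-year post procedure". For NT-proBNP the same section says: "NT-proBNP serum levels will be determined prior to the procedure, at 24 hours, and repeated after 1 year".
- **Section 2.9, Participation timeline.** The day-0 block includes blood for inflammatory biomarkers, listed ahead of the ablation, and does not name NT-proBNP. The visits at months 1, 3 and 6 list no blood draw. Month 12 lists both the inflammatory markers and NT-proBNP. No 24-hour collection appears.

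The primary objective (section 1.2) relates CMR fibrosis to "inflammatory biomarkers, and the risk of AF recurrence post catheter ablation". The Discussion wants the markers validated "as predictors of AF recurrence in patients who are scheduled for catheter ablation".

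**The concern.** A marker meant to predict recurrence in patients scheduled for ablation has to be measured before the ablation. Staff who work from section 2.3 would draw the first sample afterwards, and a pre-ablation sample that was never taken cannot be recovered at analysis. Staff who work from section 2.6.1 or 2.9 would draw on day 0 and take no 24-hour inflammatory sample. The recurrence and no-recurrence groups could then be compared on values taken at different times relative to the procedure.

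The two times need not measure the same thing. A sample taken a day after ablation may carry the response to the lesions as well as the patient's prior inflammatory state. The inclusion criteria allow radiofrequency and cryoablation, so that response may also differ by technique.

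**Working it through.** The article gives no figure for this point, so the check sets the stated times side by side.

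**Inflammatory markers (hsCRP, MMP-9, IL-6)**

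| Place | Before ablation | 24 hours | 1 year |
|---|---|---|---|
| Abstract, opening | yes | yes (immediate post-ablation) | not stated |
| Abstract, list | not listed | yes | yes |
| Section 2.3 | not listed | yes | yes |
| Section 2.6.1 | yes (baseline) | not listed | yes |
| Section 2.9 | yes (day 0, listed before ablation) | not listed | yes |

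**NT-proBNP**

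| Place | Before ablation | 24 hours | 1 year |
|---|---|---|---|
| Abstract, body text | yes | not stated | not stated |
| Abstract, list | not listed | yes | yes |
| Section 2.3 | not listed | yes | yes |
| Section 2.6.1 | yes | yes | yes |
| Section 2.9 | not named on day 0 | not listed | yes |

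1. *Could baseline in section 2.6.1 simply mean the 24-hour sample?* No. That section gives NT-proBNP three separate times, with the pre-procedure and 24-hour draws named apart, and gives the inflammatory markers two. The authors separate the two occasions where they intend both. The label still needs tightening, because section 2.9 puts the ablation itself in the day-0 block and only the order of the list shows that blood comes first.

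2. *Does any one place state all three times?* For NT-proBNP, section 2.6.1 does. For the inflammatory markers none does. The abstract's opening comes closest, but sections 2.3, 2.6.1 and 2.9 each leave out one of the two early draws.

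3. *Does the article say which draw is compared between the groups?* No. Section 2.5 defines the groups by recurrence at 1 year and section 2.13 names two-group tests, without tying either to a sampling time. That choice could ordinarily wait for an analysis plan. Here the document does not settle which samples will exist to choose from.

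4. *Can the effect of using a 24-hour value be sized?* Not from this document. It gives no biomarker means or variances, before or after ablation. Its only power statement, "a sample size of 50 patients in each subgroup has a 90% power to detect an increase in MACE-free rates proportion of 0.29", concerns a difference in proportions and supplies no standardised difference for a biomarker.

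**The case against.** The strongest reply is that the passages add up. Neither section 2.3 nor the abstract's list says that 24 hours and 1 year are the only draws. The list in section 2.3 is visibly incomplete for NT-proBNP, which section 2.6.1 also takes before the procedure, so its silence on a pre-ablation inflammatory draw is weak evidence that none is planned. Three places point to an early draw (the abstract's opening, sections 2.6.1 and 2.9). Read together, the schedule would be day 0, 24 hours and 1 year. Figure 1, which is not available here, may show it.

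Much of this stands: the cumulative reading is possible and may be what was intended. But no section states it for the inflammatory markers, and section 2.3 introduces its list as what will be determined in all patients. A figure could show the intended schedule, but the text would still disagree with itself.

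Three stronger readings are tempting and are not supported.

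- *That the 24-hour sample is a mistake.* The abstract deliberately includes the immediate post-ablation period, and the article does not state its hypothesis as one about pre-existing inflammation. It applies that term to fibrosis.
- *That the 1-year value will be used as a predictor.* No section proposes this. It would be a poor predictor, since it is taken once the groups are determined, and the Discussion itself reports higher markers in patients with AF than in those in sinus rhythm. A clarifying sentence is enough.
- *That a stated share of the effect or power is lost to procedural noise.* Any such figure would need a variance ratio and a standardised difference that the document does not give, and would have to assume that the procedural response is unrelated to recurrence.

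**Conclusion.** The point holds as an internal contradiction in the current text. It covers the sampling times of all three inflammatory markers and, to a lesser degree, NT-proBNP. It goes beyond missing detail: one version, followed as written, yields no pre-ablation value for an exposure named in the primary objective.

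That consequence is conditional. It arises if section 2.3 governs and does not arise under the cumulative reading. That a 24-hour value may partly reflect the procedure and the technique is a reasonable inference that the document neither states nor quantifies, so no size is put on it.

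**What to change.** Reconcile the abstract and sections 2.3, 2.6.1 and 2.9 to one schedule for hsCRP, MMP-9, IL-6 and NT-proBNP: day 0 before ablation, 24 hours after it, and 12 months. In section 2.9, add NT-proBNP to the day-0 list, state that the day-0 blood is drawn before the procedure, and add the 24-hour collection.

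Name the pre-ablation value as the predictor compared between the recurrence groups. Analyse the 24-hour value, or its change from day 0, separately as the early post-procedural response. As a clarification, state that the 12-month values, taken after the outcome period, are not used as predictors.

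The cost is protocol wording. The day-0 inflammatory draw is already in section 2.9, and the pre-procedure NT-proBNP is already in section 2.6.1. At most, sites working from section 2.6.1 or 2.9 add one 24-hour sample for the inflammatory markers, which section 2.3 already requires.
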